## Abstract

**Background:**

There is increasing evidence of weight regain in patients after bariatric surgery (BS), generally occurring from 12 to 24 months postoperatively. Postoperative exercise has been suggested to ad long-term weight maintenance and to improve physical function in BS patients. However, there are a limited number of intervention studies investigating the possible benefits of exercise in this population. The aim of the current report is to provide a comprehensive CERT (Consensus on Exercise Reporting Template)-based description of the rationale and details of the exercise programme implemented in the EFIBAR Study (*Ejercicio FÍsico tras cirugía BARiátrica*), a randomised controlled trial investigating the effects of a 16-week supervised concurrent (aerobic and strength) exercise intervention program on weight loss (primary outcome), body composition, cardiometabolic risk, physical fitness, physical activity and quality of life (secondary outcomes) in patients with severe/morbid obesity following bariatric surgery.

**Methods:**

A total of 80 BS patients [60–80% expected women, aged 18 to 60 years, body mass index (BMI) ≥ 40 kg/m^2^ or ≥ 35 kg/m^2^ with comorbid conditions)] will be enrolled in the EFIBAR Randomized Control Trial (RCT). Participants allocated in the exercise group (*n* = 40) will undertake a 16-week supervised concurrent (strength and aerobic) exercise programme (three sessions/week, 60 min/session), starting 7 to 14 days after surgery. The rationale of the exercise programme will be described following the CERT criteria detailing the 16 key items. The study has been reviewed and approved by the Ethics Committee of the Torrecárdenas University Hospital (Almería, Spain) (ref. N° 76/2016).

**Discussion:**

The present study details the exercise programme of the EFIBAR RCT, which may serve: 1) exercise professionals who would like to implement an evidence-based exercise programme for BS patients, and 2) as an example of the application of the CERT criteria.

**Trial registration:**

The trial was prospectively registered at Clinicaltrials.gov NCT03497546 on April 13, 2018.

**Electronic supplementary material:**

The online version of this article (10.1186/s12893-019-0566-9) contains supplementary material, which is available to authorized users.

## Background

Bariatric surgery (BS) is an effective weight loss intervention for morbidly obese patients, being successful in the treatment of obesity (stage I and II) and different associated diseases [1]. Nevertheless, there is increasing evidence of weight regain in patients after BS, [2, 3] usually occurring between 12 and 24 months postoperatively [4, 5]. Weight regain increases the risk of physical function decline, which negatively affects the functionality of an individual to carry out tasks of daily life [5]. Weight regain also increases the likelihood of obesity-related comorbidity relapse [6], which makes it necessary to implement strategies to improve the lifestyle before [7] and after BS [8].

Postoperative lifestyle interventions combining diet, exercise and behaviour modification have proven successful in aiding long-term weight maintenance and improving physical function in BS patients [9]. However, there are a limited number of intervention studies investigating the possible multidimensional benefits of exercise in this population. For patients who have undergone BS and experience suboptimum weight loss, exercise could be an important adjunct therapy [10, 11]. A previous review found a positive effect of exercise on anthropometric measurements, cardiovascular risk factors and physical fitness in BS patients [12], although results were not consistent, with a wide range of exercise programmes and perioperative timing, therefore hampering adequate practical guidance. Despite this heterogeneity, authors concluded that a beneficial exercise programme should last for a median of 12 weeks, have a mean intensity of 65% peak heart rate/VO_2max_, and be at least partially supervised [12]. A recent metha-analysis concluded that exercise training programs performed after BS were effective to optimize weight loss and fat mass loss and to improve physical fitness, although no additional effect on lean body mass loss was found [13].

In particular, strength training increases muscular strength and attenuates muscle atrophy in obese adults adhering to caloric restriction for weight loss [14, 15], whereas aerobic training provides several metabolic improvements, such as attenuating the appearance of arterial stiffness [16]. Unfortunately, it is difficult to assess the appropriate type and amount of exercise in BS patients, as it is a relatively understudied population and a variety of training regimes have been described. To date, published evidence supports a potential role for exercise to elicit positive changes in body composition after BS. However, properly designed exercise-based randomised controlled trials (RCT) are needed to provide further evidence of the effectiveness of exercise as a feasible adjunct therapy to BS [17].

In general, descriptions of exercise intervention programmes in clinical research have traditionally been vague, often containing insufficient information to allow for replication. To address this, The Consensus on Exercise Reporting Template (CERT) was recently developed to standardise the reporting of exercise intervention programmes regardless of the population [18] CERT recommends that exercise programmes published in the literature should ideally report all of the components considered in the intervention, since these are essential to evaluate the effects of clinical trials, and the interpretation, translation and implementation of research findings into clinical practice. The Consensus provides guidance on a minimum set of 16 key items required to report replicable exercise programmes. While its development was stimulated by a metaepidemiological review of exercise interventions for chronic health conditions [19] it is equally applicable to describe exercise interventions for acute conditions, injury prevention or general health. Additionally, a recent report highlighted the importance of describing exercise programs following CERT recommendations, to facilitate the replicability of these programs in BS population [20].

The aim of the current report is to provide a comprehensive CERT-based description of the rationale and details of the exercise programme implemented in the EFIBAR (*Ejercicio FÍsico tras cirugía BARiátrica*) study, a 1-year RCT investigating the effects of a 16-week supervised concurrent (aerobic and strength) exercise intervention program on weight loss (primary outcome), body composition, cardiometabolic risk, physical fitness, physical activity and quality of life (secondary outcomes) in patients with severe/morbid obesity following bariatric surgery.

## Methods/design

### Study design

Briefly, a total of 80 BS patients [60–80% expected women, aged 18 to 60 years, body mass index (BMI) ≥ 40 kg/m^2^ or ≥ 35 kg/m^2^ with comorbid conditions)] will be enrolled in the EFIBAR Randomized Control Trial (RCT) (ClinicalTrials.gov ID: NCT03497546), following recruitment from a public hospital and a private clinic in Almería, southern Spain. Participants will be randomised either to a normal care Control Group (*n* = 40), involving nutritional status monitoring and diet/physical activity counselling following international guidelines [21], or an Exercise Group (*n* = 40), who will additionally undertake a 16-week supervised concurrent (strength and aerobic) exercise programme (three sessions/week, 60 min/session) starting 7 to 14 days after surgery, with the final aim of evaluating the effects on weight loss (primary outcome), body composition, cardiometabolic risk, physical fitness and quality of life (secondary outcomes). Recruitment of participants started in May 2018 and it may extend till December 2020.

Sample size calculations indicate that, assuming an alpha error of 0.05 and a power of 80%, a total of 66 patients (*n* = 33 patients per group) will be needed to detect an effect (between group difference) of at least 0.7 standard deviations [22] in the main outcome (% total weight loss, %TWL). Anticipating a potential lost to follow-up of up to 20%, a total of 80 patients will be recruited. Additionally, we will aim at maximizing the adherence and minimizing lost to follow-up, which could in fact increase the power to detect the main effect.

The rationale of the exercise programme implemented in EFIBAR will be described following the CERT criteria recommendations for detailing the 16 items (Table 1). The structure that was followed to describe the exercise programme is presented in the Fig. 1.

**Table 1 Tab1:** CERT checklist from EFIBAR study exercise programme

	Item	Checklist Item	Identification (section)
WHAT: materials	1	Detailed description of the type of exercise equipment	Additional file 1: Table S1
WHO: provider	2	Detailed description of the qualifications, expertise and/or training	Exercise programme characteristics
HOW: delivery	3	Describe whether exercises are performed individually or in a group	Exercise programme characteristics
	4	Describe whether exercises are supervised or unsupervised; how they are delivered	Exercise programme characteristics
	5	Detailed description of how adherence to exercise is measured and reported	Programme adherence Tally sheet/daily control (Additional file 3: Table S3)
	6	Detailed description of motivation strategies	16 reinforcement WhatsApp messages / every Friday (Additional file 3) 4 reinforcement videos / end of every month (Additional file 3)
	7a	Detailed description of the decision rule(s) for determining exercise progression	Doses: Training load/intensity
	7b	Detailed description of how the exercise programme was progressed	Doses: Training load/intensity
	8	Detailed description of each exercise to enable replication	Additional file 2: Table S2
	9	Detailed description of any home programme component	Programme adherence
	10	Describe whether there are any non-exercise components	Exercise programme rationale
	11	Describe the type and number of adverse events that occur during exercise	Tally sheet/daily control (Additional file 3: Table S3)
WHERE: location	12	Describe the setting in which the exercises are performed	Exercise programme characteristics
WHEN, HOW MUCH: dosage	13	Detailed description of the exercise intervention	Weekly volume
TAILORING: what, how	14a	Describe whether the exercises are generic (one size fits all) or tailored	Sessions structure and exercises
	14b	Detailed description of how exercises are tailored to the individual	Sessions structure and exercises
	15	Describe the decision rule for determining the starting level	Sessions structure and exercises
HOW WELL: planned, actual	16a	Describe how adherence or fidelity is assessed/measured	Programme adherence Tally sheet/daily control (Additional file 3: Table S3)
	16b	Describe the extent to which the intervention was delivered as planned	Tally sheet/daily control (Additional file 3: Table S3)

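### The 80 recruits cover a loss to follow-up of at most 17.5%, not the stated 20%; the effect on power is about one percentage point

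*Protocol article*

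**What the plan says.** The sample size is justified in one paragraph of the protocol article (Methods/design, Study design). The evaluable number comes first: "assuming an alpha error of 0.05 and a power of 80%, a total of 66 patients", split as 33 per group, "will be needed to detect an effect (between group difference) of at least 0.7 standard deviations". The outcome is percentage total weight loss. The allowance for attrition follows: "Anticipating a potential lost to follow-up of up to 20%, a total of 80 patients will be recruited". The same section gives 40 patients to each arm, and the Abstract repeats the total of 80 with 40 in the exercise group. The paragraph ends by saying that efforts to keep patients in follow-up could raise power. It names no test or formula and does not say whether alpha is one-sided or two-sided.

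**The concern.** The 80 is presented as the number that protects the required 66 when losses run as high as 20%. A reader who multiplies 80 by 0.80 gets 64. Sixty-six needed, losses of up to 20% covered, and 80 recruited therefore cannot all be true at the limit that the plan sets for itself.

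What is at stake is the accuracy of the article's only justification of the trial's size, for its primary outcome. The closing remark about better retention also reads as if 80% power were already secured at 20% loss, with anything better being a gain. In fact a small part of that better retention is needed just to reach the stated design.

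**Working it through.** **Inputs, all from the Study design section:** alpha 0.05; power 80%; difference 0.7 SD; equal arms; 66 evaluable (33 per group); loss up to 20%; 80 recruited (40 per group). Sidedness is not stated.

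**1. Reproduce the evaluable number.** For two means with a standardised difference d, the normal formula is n per group = 2 x (z for alpha + z for power)² / d².
- Two-sided: 2 x (1.960 + 0.842)² / 0.7² = 32.04, rounded up to 33 per group, 66 in total. This matches the plan.
- One-sided: 26 per group, which does not match.
- Two-sided t-test (noncentral t): 33.02 per group. At exactly 33 per group its power is 79.97%, so 33 is also consistent with a t-test calculation.

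The 66 is therefore sound, and two-sided alpha is assumed from here on.

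**2. Reproduce the recruited number.**
- Dividing by the retained fraction: 66 / (1 - 0.20) = 82.5, so 83 patients. Per arm, 33 / 0.80 = 41.25, so 42 per arm and 84 in total.
- Adding 20% to the evaluable number: 66 x 1.20 = 79.2, so 80. Per arm, 33 x 1.20 = 39.6, so 40.

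The stated 80 (40 per arm) matches only the second calculation. The article does not show its step, so this origin is inferred from the match.

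**3. What 80 recruits leave.**
- At 20% loss: 80 x 0.80 = 64, or 32 per group, two short of 66.
- Largest loss that still leaves 66: (80 - 66) / 80 = 14/80 = 17.5%.

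**4. What this does to power** (d = 0.7, two-sided alpha 0.05, equal loss in the arms).

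| Evaluable per group | Loss from 40 | Power, t-test | Power, normal approximation |
|---|---|---|---|
| 40 | 0% | 87.1% | 87.9% |
| 33 | 17.5% | 79.97% | 81.2% |
| 32 | 20% | 78.7% | 79.96% |

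The normal figure at 32 per group can be checked by hand: 0.7 x √(32/2) = 2.80; 2.80 - 1.96 = 0.84; the standard normal probability below 0.84 is about 0.80.

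By the t-test, the difference detectable with 80% power is 0.700 SD at 33 per group and 0.711 SD at 32 per group.

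**The case against.** The strongest reply is that the slip has almost no consequence. Twenty percent is worded as an upper bound, not as the expected loss, and the team says that it will work to keep losses down. The requirement of 66 is met at every loss up to 17.5%, so the conflict is confined to losses above 17.5% and up to 20%. Even at 20%, the normal approximation gives 79.96%, which anyone would report as 80%, and at the plan's one-decimal precision a detectable effect of 0.71 SD is still 0.7 SD. All of this stands, and it is why the point is minor. It does not remove the contradiction: an allowance stated to cover losses up to a limit should hold at that limit, and this one does not.

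Three stronger readings are tempting, and the documents support none of them.
- A reader might infer that the trial fails to deliver its stated power. That holds only if loss exceeds 17.5%, and then by about 1.3 points at most under the t-test with equal loss (79.97% - 78.7%).
- A reader might infer that 33 per group leaves no margin at all. That depends on the method, which the article does not name. By the t-test the requirement is 33.02, so there is none. By the normal formula it is 32.04, so rounding up to 33 already supplies nearly the one patient per group that is later missing.
- A reader might argue that losses concentrated in one arm would make matters worse. Nothing in the article suggests a particular imbalance, so any such figure would rest on an invented split.

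Nor can the matter be left to a fuller document. Nothing is said to be missing; figures printed in the same paragraph disagree.

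**Conclusion.** Wrong as written, but minor. At the plan's own limit of 20% loss, 80 recruits leave 64 evaluable patients instead of the required 66. The figure of 80 covers a loss of at most 17.5%; covering 20% would take 83 patients, or 84 with equal arms. The cost in power at 20% loss is small: 78.7% by the t-test or 79.96% by the normal approximation, against 80% stated.

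The arithmetic on 80, 66 and 20% needs no assumption. The power figures assume a two-sided alpha of 0.05, a simple comparison of two means, and equal loss in the arms. The point calls for a corrected statement. It does not show that the trial is underpowered or that its design should change.

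**What to change.** Keep the target of 80 and replace the attrition sentence with one that is true, for example: *Eighty recruits leave the required 66 if loss to follow-up is at most 17.5%; at 20% loss, 64 completers give about 79–80% power for a difference of 0.7 SD.* It would help to add that alpha is two-sided, if that is what was used, and to name the method behind the 66, so that a single power figure can be quoted instead of a range.

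The cost is one sentence and a slightly less favourable stated figure. No patients are added, and neither the design nor the analysis changes. Raising the target to 83 or 84 would also make the article's sentence about 20% loss true, but a gain of about one point in power at the worst anticipated loss hardly justifies it.

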**Fig. 1 Fig1:**
[figure not shown]
Graphical abstract of the detailed exercise programme of the EFIBAR Study

### Programme structure

#### Exercise programme rationale

With the overall aim of making this exercise programme transferable to society, the exercise level in EFIBAR is based on the physical activity recommendations for adults proposed by the World Health Organization [23], together with the American College of Sports Medicine’s position stand [24] on progression models in strength and aerobic training for healthy adults. Since there is limited information regarding the ideal exercise model for morbidly obese adults, we will combine strength and aerobic training (i.e., a concurrent training protocol), as previous findings in obese adults displayed important benefits when both strength and aerobic exercise are implemented in the same session [25]. A question that often arises is whether aerobic or strength training should be performed first within any particular training session. It has been suggested that performing aerobic exercise prior to strength training could result in impaired strength training performance (e.g., strength exercises technique), and unfavourable responses to strength (decrease in force production) when strength training is conducted with moderate to high loads in the general population [26]. Moreover, in a previous study conducted in obese men, concurrent strength prior to aerobic training generated a greater effect in reducing body fat compared to aerobic prior to strength training [27]. However, further research is still needed to know which order (i.e., strength prior to aerobic or vice versa) produces greater benefits in BS patients.

The length of the intervention period is 16 weeks based on a previous large scale RCT [28], where substantial physiological adaptations occurred within the first 3 to 6 months of exercise. We also considered the increased logistical and participation burdens, which indeed might lead to poorer adherence, as well as the cost of running a highly controlled laboratory-based study for a longer period. In addition to the exercise programme, all participants (both control and exercise groups) will undergo routine visits to the clinic during medical discharge and also for follow-up visits (months 1, 3, 6, 9 and 12). In these examinations, lifestyle-specific instructions (Item 10), including dietary and physical activity recommendations, will be provided as indicated in the perioperative clinical practice guidelines by the American Association of Clinical Endocrinologists, The Obesity Society, and American Society for Metabolic & Bariatric Surgery [29].

#### Exercise programme characteristics

The exercise programme will be carried out in a fitness room at the University of Almería (400 m^2^), which is equipped with aerobic and strength training areas. The mean temperature registered in Almería from www.aemet.es averaged 19° during 2018. The training programme will be free for participants (Item 12). The detailed description of the exercise equipment (Item 1) used in the training programme is shown in Additional file 1: Table S1. Two Personal Trainers (PT) with BSc degrees in Sport Sciences, and at least 2 years of experience as personal trainers, will be in charge of all sessions (Item 2). The PTs will receive a written standardised programme and weekly instruction by the study group training coordinators. Finally, the exercise programme will be developed individually (i.e., personal training sessions) (Item 3) and always supervised with a ratio of one-to-one (1,1, personal trainer, participant) (Item 4), unless participants report schedule unavailability; if this is the case, some sessions will be permitted to include two patients per PT.

#### Weekly volume

The prescription of the exercise programme will try to meet the recommendations proposed by current guidelines for aerobic and strength training in healthy adult populations [29]. The total exercise training volume will be 180 min/week. The doses will be composed of 48 sessions (1 h/session) over 16 weeks (3 times/week). A full description of the training periodization (Item 13) is shown in Table 2.

It is estimated that 150 min/week of moderate intensity, i.e., ≈3–5.9 metabolic equivalent (MET, 1 MET = 3.5 ml O_2_/kg/min) aerobic physical activity is equivalent to 1000 kcal/week; this is associated with lower rates of cardiovascular disease and premature mortality in healthy adults [29]. Moreover, an energy expenditure of 1000 kcal/week can also be achieved with ≈75 min/week of vigorous intensity (≥6 METs) aerobic exercise. Thus, the proposed weekly volume of 180 min/week of concurrent training is likely to elicit ≈1200 kcal/week. PTs will continuously monitor heart rate using a *Polar* Electro V-800 (Kempele, Finland) in all sessions of the intervention programme.

#### Weekly frequency

Although physical activity recommendations suggest undertaking physical activity most or preferably all days of the week, there was concern that exercising more than 3 days per week would be an excessive burden and might have undesirable effects on participants’ adherence and motivation to complete the exercise intervention programme. Studies on exercise frequency show little differences for 3 or more days per week provided the weekly dose of exercise is attained [29]. Participants in the EFIBAR study will perform the exercise programme 3 days per week (preferably on Mondays, Wednesdays and Fridays). If the participant misses one training session, the participant will be rescheduled for a different day of the week to recover the session, provided the necessary between-session resting time is achieved (a minimum of 24 h). A previous study of morbidly obese women found that three sessions per week improved cardiac parameters, such as variability and heart rate kinetic [30]. At the end of each training week, the PTs will remind participants of their appointments for the following week’s training sessions to increase attendance.

#### Sessions structure and exercises

The main structure of the physical exercise sessions will be: 1) warm up; 2) compensatory training; 3) strength training; 4) aerobic training; and 5) cool down. A detailed description of the exercises used in the EFIBAR RCT (Item 8) is shown in Additional file 2: Table S2. Briefly, the warm up comprises 5 min of low intensity aerobic activity (treadmill) at 50 to 65% of heart rate reserve (HRR). Compensatory training includes core stability and stabiliser muscle exercises prior to strength training. Strength training will comprise a whole body exercise routine involving major upper and lower body muscle groups progressed through three phases after a familiarisation phase. Then, aerobic training will be conducted on a treadmill. Finally, participants will perform a cool down including static and dynamic stretching exercises.

In compensatory training, from week 3 until the end of the programme, participants will perform nine core stability and stabiliser muscle exercises, in order to minimise risk of injury and, hopefully, increase adherence (page 30 to 59 of Additional file 2: Table S2). All exercises will be modified such that they can be performed at three levels of difficulty: basic (Level A), intermediate (Level B) and advanced (Level C). All participants will begin at the basic level (Item 15). These exercises will be carefully progressed in level of difficulty (Item 7a and 7b). In general, Level A will be carried out from week 3, Level B from week 5, and Level C from week 11. A certain degree of individualization will also be permitted, as each participant will progress through the different exercise levels (i.e., A, B or C) according to their individual adaptation; when the participant successfully complete all sets/repetitions of the prescribed exercises in a level (see Additional files 2 and 3) over more than three consecutive sessions (i.e., over 1 week), they will be able to progress to the next level. Our PTs will modify all exercises based on the participant’s response to the exercise (Item 14a and 14b)*.* The progression and order has been carefully structured, as presented in Additional file 2: Table S2. The proposed exercises allow for good activation of the central area of the body (e.g., abdominal area) with low pressure in the spinal structures (e.g., bird dog, side plank or modified crunch), as recommended in previous studies [31].

For strength training*,* the exercises will progress in intensity based on the participant’s response to the exercise during the four main phases (Item 7a and 7b): familiarisation (weeks 1 to 4), phase 1 (weeks 5 to 8), phase 2 (weeks 9 to 10) and phase 3 (weeks 11 to 16). Participants will go through a familiarisation period during the first 4 weeks of the exercise program before including external loads*.* Since participants may present some movement limitations due to discomfort during the first weeks after surgery [32], we will prescribe exercises that allow participants to learn movement patterns (from week 1) and weight-bearing and strength training with elastic bands (from week 3) of the different main movements (e.g., squat, horizontal pull, vertical push); this will provide participants with the appropriate technique for the main exercises. In this phase, participants will learn seven movement pattern exercises, which constitute the basis of movement, such as diaphragmatic or abdominal breathing, dissociation and mobility of the hip or stabilization of the shoulders or the wrist. These seven exercises can be performed whenever the PT feels they are necessary over the 16 weeks in order to remind the patients of the basic movement patterns. During the first 4 weeks, participants will perform two sets of 5 to 7 repetitions of each movement pattern exercise. The resting time between series of these exercises will be adjusted to the patients’ perceptions. Moreover, they will be asked to perform the exercises at progressively increasing speeds. It will be recommended that they do not perform trunk and hip flexion exercises until week 2 or 3 to avoid discomfort in the area of the surgical intervention (see the example of the hip flexion exercises 2 and 6 of movement pattern exercises in Additional file 2: Table S2). Likewise, in order to minimise trunk flexion during the first 2 to 3 weeks, we will avoid upward facing positions by proposing foot variants (see exercises 1 and 2 of the movement patterns exercises). Given the participants’ degree of obesity, the order of the exercises was carefully designed to improve the flow of the sessions (i.e., reducing the number of transitions from lying to standing positions). Thus, the seven proposed exercises will be performed in the order detailed in Additional file 2: Table S2.

From phase 1 (week 5) onwards, all participants will perform exercises with external loads, including six main exercises performed in the following order: 1) squat; 2) seated lat pull-down; 3) bench press; 4) seated low row; 5) push press with dumbbells; and 6) deadlift. The training progression from one exercise to another will be done vertically (e.g., exercise 1 – rest – exercise 2). A detailed description of each exercise is presented in Additional file 2: Table S2, according to previous training recommendations [4] (Item 14a and 14b). Participants will be instructed to exercise through the full range of motion and to avoid the Valsalva manoeuvre. Finally, it should be noted that previous studies used similar strength training modalities in BS populations, such as stack-weight equipment, free weights, body weight or resistive bands, in order to maintain high levels of enjoyment, engagement, and most importantly, adherence [33].

The aerobic training part will be conducted on a treadmill after strength training. Previous findings recommend that obese individuals can briskly walk or even run, provided they follow conservative transitions and progression, schedule rest days and heed onset of pain symptoms [34]. For progression to running, intensity or mileage increases should be slow and consistent to prevent musculoskeletal injury. Moreover, a study by Vincent et al. indicated that patients who have undergone bariatric surgery and are now lean can also run, but special foci, such as hydration and energy replacement, must be considered. All these considerations will be taken into account in the EFIBAR RCT.

Finally, participants will perform a cool down, including 5 min of static and dynamic stretching exercises in order to promote training adherence.

